# GET.ON Mood Enhancer: efficacy of Internet-based guided self-help compared to psychoeducation for depression: an investigator-blinded randomised controlled trial

**DOI:** 10.1186/1745-6215-15-39

**Published:** 2014-01-30

**Keywords:** Guided self-help, Internet-based, Major depressive disorder, Randomised controlled trial, Negative effects of psychotherapy, Active control

## Abstract

**Background:**

Major depressive disorder (MDD) imposes a considerable disease burden on individuals and societies. A large number of randomised controlled trials (RCTs) have shown the efficacy of Internet-based guided self-help interventions in reducing symptoms of depression. However, study quality varies considerably. The aim of this study is to evaluate the efficacy of a new Internet-based guided self-help intervention (GET.ON Mood Enhancer) compared to online-based psychoeducation in an investigator-blinded RCT.

**Methods/design:**

A RCT will be conducted to compare the efficacy of GET.ON Mood Enhancer with an active control condition receiving online psychoeducation on depression (OPD). Both treatment groups will have full access to treatment as usual. Adults with MDD (*n* = 128) will be recruited and randomised to one of the two conditions. Primary outcome will be observer-rated depressive symptoms (HRSD-24) by independent assessors blind to treatment conditions. Secondary outcomes include changes in self-reported depressive symptom severity, anxiety and quality of life. Additionally, potential negative effects of the treatments will systematically be evaluated on several dimensions (for example, symptom deteriorations, attitudes toward seeking psychological help, relationships and stigmatisation). Assessments will take place at baseline, 6 and 12 weeks after randomisation.

**Discussion:**

This study evaluates a new Internet-based guided self-help intervention for depression using an active control condition (psychoeducation-control) and an independent, blinded outcome evaluation. This study will further enhance the evidence for Internet-based guided self-help interventions for MDD.

**Trial registration:**

German Clinical Trial Registration (DRKS): DRKS00005025

## Background

Major depressive disorder (MDD) is one of the most prevalent psychiatric disorders with a lifetime prevalence of more than 16% [1-3]. Moreover, MDD is related to a considerable quality of life decrement [4,5], increased mortality rates [6], and substantial economic costs [7-9]. Currently, MDD ranks as the fourth disorder with the highest disease burden and is projected to be the leading cause of disability in high-income countries by 2030 [10].

Although there is ample evidence for the effectiveness of psychotherapy in the treatment of depression [11,12], many individuals remain untreated [13]. People who could particularly benefit from treatment disregard treatment for several reasons including a lack of knowledge of what to do, prohibitive costs, anticipated negative (social) consequences or preference for self-help [14]. Moreover, those seeking help hardly receive immediate access to evidence-based treatment because of long waiting lists for psychotherapeutic treatment [14,15]. Limited availability of clinicians, geographical inaccessibility and difficulties to ‘attend therapy during usual business hours’ are further barriers.

Using the Internet to provide guided self-help interventions may help to overcome some of the limitations of traditional treatment services. Internet-based guided self-help strategies have several advantages over face-to-face approaches. These include: (1) interventions are more easily accessible at any time and place; (2) anonymity is assured when patients want to avoid stigmatisation; (3) a greater potential for the integration of acquired skills in daily life exists because of an emphasis on the participants’ active role in (guided) self-help interventions [16]; (4) participants can work at their own pace and go through materials as often as they want; (5) travel time and costs for both participants and clinicians are eliminated; (6) Internet-based interventions may attract people who do not (want to) make use of traditional mental health services [17]; and (7), Internet-based interventions are easily scalable, implying that only a small increase of therapeutic resources is required for reaching a greater proportion of the eligible population using these interventions.

Accumulating empirical evidence suggests that Internet-based interventions are well-accepted by participants [18] and effective in the treatment of MDD [19], subthreshold depression [20] and as maintenance treatment [21]. A systematic review of 19 randomised controlled trials (RCTs) evaluating Internet-based interventions for symptoms of depression in 2,996 individuals [19] found a mean effect size of d = 0.56. Interventions including at least some guidance by a clinician were more effective (d = 0.78) than interventions without guidance (d = 0.36). Cuijpers (2010) showed that guided self-help interventions for depression (and anxiety disorders) could have comparable effects to traditional face-to-face therapy even when they are directly compared to each other [22].

However, a recent methodological analysis of 75 RCTs of computer- and Internet-based interventions for psychiatric disorders [23] criticised the mean methodological quality of published trials in the field as rather low. They criticised, for example, that many studies used weak control conditions (that is, wait-list control), that most studies relied solely on participants’ self-report, and that they failed to include an independent assessment such as blind ratings or biological indicators. Moreover, they found that low overall methodological quality scores were associated with higher reported effect sizes. In fact, the latest systematic review in the field on Internet-based treatments for depression [19] did not include any study that used an independent outcome assessment by assessors blind to the treatment condition. Moreover, half of the included studies used a wait-list control-only comparison. To the best of our knowledge no study on Internet-based treatment for major depression published so far, has applied an independent, blinded outcome evaluation.

Another important issue not adequately addressed to date is the potential negative effects of Internet-based treatments for depression. One particularly unfavourable outcome of psychotherapy is deterioration of symptoms during treatment. However, RCTs evaluating psychological treatments seldom report the number of patients who had deteriorated while being treated [24]. Critics of Internet-based treatments have often emphasised that treatment might be provided that is less intensive than required to treat severely affected or symptomatic individuals [23]. This inadequate treatment allocation may result in less treatment expectations for psychotherapy in general and discourage individuals from seeking more intensive treatment. Hence, not only is there a pressing need for research on potential adverse events of psychotherapy in general [24] but also specifically for Internet-based treatments.

### Objective and research questions

The aim of this study is to evaluate the efficacy of a newly developed guided self-help Internet-based intervention (GET.ON Mood Enhancer) compared to an online psychoeducation on depression (OPD).

We expect that observer-rated depressive symptomatology assessed by raters blind to treatment conditions will be reduced to a greater extent in the intervention group than in the control condition. Moreover, we hypothesise that GET.ON Mood Enhancer is superior in terms of self-reported depressive symptoms, wellbeing, quality of life, symptoms of anxiety and problem-solving skills compared to the OPD-control condition. Potential negative effects with regard to (1) numbers of patients with symptom deteriorations, (2) attitudes towards seeking psychological help, and (3) other adverse events will be systematically evaluated. We hypothesise that both treatment conditions will not have a negative effect on attitudes towards seeking psychological help.

## Methods/design

### Design

A two-arm RCT will be conducted to compare GET.ON Mood Enhancer with an online psychoeducation on depression (OPD) condition. Both treatment arms will have full access to treatment as usual. Assessments will take place at baseline (T1), post-treatment (6 weeks, T2) and 12-week follow-up (T3; see Figure 1 for a detailed overview of assessments). All procedures involved in the study will be consistent with the generally accepted standards of ethical practice approved by the University of Marburg ethics committee (No. 2013–08 K). The trial is registered in the German clinical trials register under DRKS00005025.

**Figure 1 F1:**
[figure not shown]
Study flow.

### Trial status

By the time of submission, recruitment for the trial was still ongoing. Recruitment started in June 2013 and will approximately last until February 2014.

### Participants and procedure

#### Inclusion and exclusion criteria

We will include adults (1) above the age of 18 years (2) with MDD according to DSM-5 criteria (3) who have Internet access, (4) have sufficient German skills in reading and writing (self-report), and (5) are willing to give informed consent. We will exclude subjects (1) with a history of manic/hypomanic episodes, (2) with a history of psychotic disorders, (3) currently receiving psychotherapy for any kind of mental health problems, (4) showing a notable suicidal risk as indicated by a score greater than 1 on BDI Item 9 (‘I feel I would be better off dead’), or (5) a change in antidepressive medication dosage/drug within 4 weeks before baseline.

#### Recruitment

Participants will be recruited via the GET.ON research website [25] that is announced in newspapers, on-air media and related websites. The research website provides information about the GET.ON Mood Enhancer training and details about another study evaluating GET.ON Mood Enhancer in a sample with subthreshold depression (Trial registration: DRKS00004709, [26]). Those participants who do fulfil criteria for a MDD are excluded from that study, and instead offered to participate in this trial.

#### Assessment of eligibility and randomisation

People who apply for study participation will receive an information letter with detailed information about the study procedures. Full written informed consent will be obtained from all participants. They will be informed that they can withdraw from the intervention and/or study at any time without any negative consequences. Nevertheless, we will ask those who withdraw from the trial treatment to attend all the remaining research appointments or at least provide minimal data (primary outcome measure). Applicants who continue to participate in the study will be asked to complete online screening questionnaires to assess the severity of their depressive symptoms (CES-D >16), whether they are currently receiving any kind of treatment for any mental health disease and whether they have a high suicidal risk (BDI Item 9 > 1). Subjects screened positive and are willing to give informed consent will be scheduled for a structured clinical interview (SCID) conducted via the telephone [27]. SCIDs will be conducted by trained clinicians. Participants meeting all of the inclusion and none of the exclusion criteria, who have completed the baseline assessment, and returned the informed consent form will enter the study and will be randomly allocated to study conditions. Randomisation will take place at an individual level. The allocation will be performed by an independent researcher not otherwise involved in the study using an automated computer-based random integer generator (randlist). The allocation will be concealed in advance from participants, researchers involved in recruitment, and therapists.

#### Assessments

Self-report and observer-rated assessments will take place at baseline, post-intervention and 12-week follow-up. See Figure 1 for a detailed overview. Self-report data will be collected using a secured online-based assessment system (AES, 256-bit encrypted), and observer-based assessments will be conducted via the telephone by trained interviewers. Observer-rated assessments will be recorded to examine inter-rater reliability. In case of disagreement, the two raters will discuss until a consensus is formed, and the agreed rating will be used for analysis. If no agreement is reached after discussion, the assessment will be rated by an experienced diagnostic-rater (gold standard), and this rating will be used for analysis.

#### Blinding

The research staff conducting the observer-based rating of depressive symptoms will be blinded to the condition the participants are assigned to. Considerable effort is undertaken to ensure blindness, including (1) an explanation to the participants why it is important not to inform the interviewer about the condition they were assigned to, (2) a written reminder in the interview manual for the interviewer to ask the participant not to mention anything about their randomisation status, (3) verbal reminders to the patient before the interview, and (4) a documentation after the assessment of whether or not the interviewer is still blind to the treatment condition. In the event of a blind violation, the interviewer will be changed to the following assessment. Participants know about the content of both conditions, but are blinded with regard to which intervention is the experimental and which the control condition.

### Intervention

#### GET.ON Mood Enhancer

GET.ON Mood Enhancer is a brief intervention consisting of six lessons with modules concerning psychoeducation, behavioral activation (BA), problem solving (PS) and relapse prevention. Additionally, participants are offered four modules that can be chosen based on individual need and/or preference. Additional modules are directed at sleep problems, relaxation techniques and dealing with worrying thoughts (see Table 1 for a session overview). Lessons consist of text, exercises and testimonials and also include interactive elements such as audio and video clips. A strong focus of the intervention lies on transfer tasks (homework assignments) to integrate newly acquired strategies and techniques into daily life. In the beginning of each subsequent lesson, participants are invited to reflect on their experiences with the newly acquired skills. The training is adaptive as the content is tailored to the specific needs of the individual participant by continuously asking participants to respond by choosing among various response options. Subsequent content is then tailored to the participant’s response. Using responsive web design, participants can follow the program on the Internet, a tablet or mobile phone. An integrated read-aloud function allows participants to follow narrated lessons. Participants are advised to complete at least one but preferably two lessons per week, because a previous meta-regression analysis about the role of treatment intensity for treatment outcome in the treatment of depression indicated that more frequent therapy sessions might be associated with a better outcome compared to a lower frequency of sessions [28]. Consequently, the training lasts about 3 to 6 weeks. We decided that we will not include more modules, because (1) a recent meta-analysis [19] found that web-based interventions for depression including more than seven modules were less effective (d = 0.36) than interventions with seven or less modules (d = 0 .75), and (2) we want to lower the threshold for individuals as much as possible. In terms of a stepped-care model participants will be encouraged to seek more intensive help in routine mental health services, if their progress is not sufficient at the end of the intervention. During the last treatment session, they will be provided with information about evidence-based treatments in routine mental healthcare and how to obtain access to it.

**Table 1 T1:** Overview of GET.ON Mood Enhancer lessons

**Session**	**Topic**	**Content**
1	Psychoeducation	• Information about symptoms, causes and types of depression
		• Role of motivation
		• Introduction of the mood and activity diary
2	Behavioural activation (BA) I	• Relationship between activities and depression
		• Introduction of daily activity scheduling
3	Behavioural activation (BA) II	• Reflection on experiences with newly acquired skills and on activities/behaviour that might have influenced the mood (from now on in every session at the beginning)
		• Coping with difficulties with regard to daily activity scheduling
		• Goal setting for the upcoming days
		• Additional: sleeping problems
4	Problem-solving techniques (PST) I	• BA: reflection of goal attainment and goal setting for the upcoming days
		• PST: distinction between solvable and unsolvable problems
		• PST: introduction of 6-step PST procedure: (1) defining the problem, (2) defining the goal, (3) brainstorming about possible solutions and choosing the best one, (4) making a plan how to implement this solution, (5) putting the solution into practice, and (6) evaluating the outcome.
		• PST: choosing one personal problem, filling out steps 1 to 4, step 5 as homework
5	Problem-solving techniques (PST) II	• BA: reflection of goal attainment and goal setting for the upcoming days
		• PST: deepening the 6-step procedure: step 6 of the 6-step procedure: evaluating outcome; depending on the evaluation: coping with difficulties, revising steps 1 to 4 or choosing another problem
		• Additional: stop-worrying techniques
6	Relapse prevention	• BA: reflection goal attainment and goal setting for the future
		• PST: step 6 of the 6-step procedure: evaluating outcome
		• Evaluation: summarising gains and learned strategies
		• Developing an individual relapse prevention plan
		• Information about further healthcare services

The main modules used in GET.ON Mood Enhancer are based on evidence-based face-to-face manuals that have been found to be effective in the treatment of depression, such as behaviour therapy (BT) [29] and problem-solving therapy (PST) [30]. In BT, a strong focus rests on daily pleasurable activity scheduling that is integrated in each lesson. The PST elements implemented in GET.ON Mood Enhancer have been used in various web-based interventions, such as the Dutch web-based ‘Alles onder Controle’ course, which has been shown to be effective in reducing depressive symptomatology across several RCTs [31,32].

During the training, participants will be supported by an online therapist. Every participant will be assigned to one therapist for the duration of the study. The total time a therapist spends on a participant will be approximately 2 to 3 hours. Guidance is provided by psychotherapists in training supervised by an experienced clinician. Participants will communicate with their therapist through the internal messaging function of the system on which GET.ON Mood Enhancer is implemented. The guidance is mainly based on the supportive-accountability model of providing guidance in Internet-based interventions [33]. In the current study, the purpose of the guidance will be to support participants to adhere to the treatment modules, and therapists will not teach therapeutic techniques beyond techniques used in the treatment modules. All feedback from therapists is stored for supervision and adherence checks.

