**OPD**
*)*
**

The OPD intervention is also Internet-based and is implemented on the same platform as GET.ON Mood Enhancer. In the current study, the psychoeducational intervention is based on the patient version of the German S3-Guideline/National Disease Management Guideline Unipolar Depression [34]. It informs participants about the nature and evidence-based treatments of depression including information about symptoms, strategies to overcome depression and sources of help. In this study, the psychoeducational intervention requires no explicit homework assignments from the participants and provides no therapist support. Passive psychoeducational interventions have been shown to be effective in reducing depressive symptoms with a pooled standardised effect size of d = 0.26 [35].

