### Sample size calculation

We aim to include 128 participants. This sample will allow us to detect a between-group effect size (ES) of d = 0.50 with a power (1-ß) of 80% and an alpha of 0.05 (calculated using PASS 12). The most recent meta-analytic review found a mean ES of d = 0.78 for therapist-supported web-based interventions for depression [19]. However, most of the included studies used a waiting-list control comparison only, and these studies showed a considerably larger ES than those studies including a treatment-as-usual condition. Our comparison condition will include psychoeducation and full access to treatment as usual and participants are encouraged to seek further help. Thus, we expect a somewhat smaller ES of d = 0.50 at post-treatment.

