### Statistical analyses

The clinical trial will be conducted in compliance with the Declaration of Helsinki, the CONSORT guidelines, GCP and the protocol. Aiming at an intention-to-treat design [61] we will include all participants who will be randomly assigned to one of the two conditions. Additional per protocol analyses (PPA) will be conducted, including only participants’ satisfying protocol treatment (completed at least 4 of 6 modules). Mixed-model analyses of variance will be conducted to explore the effects of the treatments on all continuous outcomes. Missing data will be handled using multiple imputations (MI). MI is especially robust with respect to missing data [62]. Nevertheless, to assess systematic effects of non-ignorable missing data, pattern mixture analyses for multi-level longitudinal approaches [63] will be conducted. To determine if the treatment effect is dependent on missing data, the missing-data pattern of each participant will be first coded and then included in a three-way interaction (missing pattern × condition × change in depression severity) in the main outcome analyses. If no significant interactions between missing-data pattern and treatment outcome are found, we will conclude that no missing data bias occurred in the results. For all mixed-model analyses, Cohen’s d [64] will be calculated by standardising the differences between baseline and follow-up scores by the pooled standard deviation of the baseline scores. Response and remission rates will be compared across groups with the help of contingency tables and χ2 tests. We will also calculate the number needed-to-be-treated (NNT) with GET.ON Mood Enhancer to achieve one response and remission, respectively, compared to the control group. We will also calculate the number needed-to-harm, which indicates the number of participants treated in the experimental condition for one extra person to have a symptom deterioration. Because the differential risk of the intervention ideally needs to be set into relation with its benefits we will also calculate a benefit-risk ratio [65]. Benefit-risk ratio will be calculated by dividing the NNH to achieve one symptom deterioration through the NNT to achieve one response. If this benefit-risk ratio is greater than 1, the benefits outweigh the risks; if it is 1, the balance between benefit and risks are equal across the groups; if it is less than 1, the risks outweigh the benefits (LIT). Benefit-risk ratios will only be calculated when differences in risk for symptom deteriorations are statistically significant.

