
For other negative effects, we will use independent t-tests for continuous, χ^
*2*
^ for categorical, and logistic regression for binary outcomes. In a pre-planned subgroup analysis, we will explore negative effects of GET.ON Mood Enhancer on attitudes towards seeking psychological help in patients who do not reach the response criteria up to post-assessment (6 weeks). For all statistical analyses, significance level will be set at *P* <0.05. All analyses will be conducted using SPSS 20.

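### The 80% power at N = 128 makes no allowance for therapist clustering in the GET.ON arm, and the analysis text names no therapist term

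*Protocol article*

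**What the plan says.** The protocol article, under GET.ON Mood Enhancer, states that "Every participant will be assigned to one therapist for the duration of the study". The support comes from supervised trainee psychotherapists through the platform's messaging function and takes roughly 2 to 3 hours per participant. The section on the psychoeducation condition says that OPD "provides no therapist support". Randomisation is by individual.

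Under Sample size calculation: "We aim to include 128 participants", then "This sample will allow us to detect a between-group effect size (ES) of d = 0.50 with a power" of 80% at alpha 0.05, and the basis is given as "Thus, we expect a somewhat smaller ES of d = 0.50 at post-treatment". No ICC, number of therapists, caseload or design effect appears there.

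Under Statistical analyses: "Mixed-model analyses of variance will be conducted to explore the effects of the treatments on all continuous outcomes". That section goes on to specify multiple imputation, pattern-mixture analyses, effect-size standardisation, NNT and NNH. It does not mention therapist, and it lists no random effects of any kind.

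**The concern.** One arm is treated by a set of therapists and the other by none, so this is a partially nested design despite individual randomisation. Participants who share a therapist may have more similar outcomes than participants who do not. If so, the GET.ON mean varies more than 64 independent observations would imply.

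Two things follow when the within-therapist correlation is positive. The power at a fixed N is below the figure computed for independent observations. An analysis that leaves therapist out gives intervals that are too narrow and a type I error above 5%, and the error always runs in that direction. The comparison affected is the primary one, HRSD-24 at 6 weeks, in a trial that presents methodological rigour as its main contribution.

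**Working it through.** **Inputs from the protocol article.** Total N = 128; d = 0.50 at post-treatment (so SD = 1); power 80%; alpha 0.05; one therapist per GET.ON participant; no therapist in OPD.

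**Assumptions, because the article does not give them.** Two-sided test; 1:1 allocation (64 per arm); k therapists with equal caseloads m = 64/k; therapist ICC of 0.02 or 0.05; total variance 1 in each arm; no dropout; a single post-treatment comparison without baseline adjustment.

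**Step 1: reproduce the stated N.** A two-sided two-sample t-test (noncentral t) has power 79.5% with 63 per arm and 80.1% with 64 per arm, so 64 per arm, or 128 in total, is the smallest balanced N that reaches 80%. A one-sided test would need only 50 per arm by the normal formula. The stated figure is therefore the independent-observations N, with nothing added. In the normal approximation used below, the same case is Φ(0.5/√(2/64) − 1.96) = 80.7%, and this is the reference value for the power column.

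**Step 2: add one-arm clustering.**

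- Design effect in the GET.ON arm: DE = 1 + (m − 1) × ICC
- True SE = √(DE/64 + 1/64); SE under independence: SE₀ = √(2/64) = 0.1768
- Power = Φ(0.5/SE − 1.96)
- Type I error if therapist is ignored = 2 × [1 − Φ(1.96 × SE₀/SE)]

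Worked case, k = 4 and ICC = 0.05: m = 16; DE = 1 + 15 × 0.05 = 1.75; SE = √(2.75/64) = 0.2073; SE/SE₀ = 1.173; power = Φ(2.412 − 1.96) = 67.4%; type I error = 2 × [1 − Φ(1.671)] = 9.5%.

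| Therapists (k) | m | ICC | DE | SE/SE₀ | Power | Type I error |
|---|---|---|---|---|---|---|
| any | – | 0 | 1.00 | 1.000 | 80.7% | 5.0% |
| 4 | 16 | 0.02 | 1.30 | 1.072 | 75% | 6.8% |
| 4 | 16 | 0.05 | 1.75 | 1.173 | 67% | 9.5% |
| 8 | 8 | 0.02 | 1.14 | 1.034 | 78% | 5.8% |
| 8 | 8 | 0.05 | 1.35 | 1.084 | 74% | 7.1% |
| 12 | 5.33 | 0.02 | 1.09 | 1.021 | 79% | 5.5% |
| 12 | 5.33 | 0.05 | 1.22 | 1.053 | 77% | 6.3% |

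Putting the t critical value (1.979 on 126 df) into the same normal formula gives slightly lower type I errors: 6.5% / 9.1%, 5.6% / 6.8% and 5.3% / 6.0% for 4, 8 and 12 therapists. That variant gives 4.8% rather than 5% at ICC = 0, so the table uses 1.96.

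**Step 3: where it stops mattering.** With k = 16 and ICC = 0.01, DE = 1.03, the SE is 0.7% larger and power is 80.2% against 80.7%.

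**Step 4: what small-sample degrees of freedom add.** A Satterthwaite df built from k − 1 and 63 lowers power further, for example to 65% (k = 4, ICC 0.02) and 70% (k = 8, ICC 0.05). The same rule already gives only 73% (k = 4) and 78% (k = 8) at ICC = 0. Part of that loss is therefore the price of a conservative df rule and not an effect of clustering, and these figures are kept out of the table.

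**Step 5: baseline adjustment.** HRSD-24 is also measured at baseline. If baseline is a covariate with correlation r to the outcome, both variance terms are multiplied by 1 − r², taking the ICC as unchanged. With an assumed r = 0.5, power is 86% (k = 4, ICC 0.02), 79.5% (k = 4, ICC 0.05) and 85% (k = 8, ICC 0.05). With r = 0.3 these become 79%, 72% and 78%. Under this scaling SE/SE₀ does not change, so the type I error column stays as it is.

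**The case against.** A reader might infer more than the document supports: that the planned mixed models treat all 128 participants as independent, that their standard errors are too small, and that 80% power is not delivered. The case against that reading is strong.

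- **Silence is not independence.** The article names a mixed model without listing any random effects. That structure is commonly left to the analysis plan, which is not shown. The text does not exclude a therapist term. This stands: one can say only that no such term is named.
- **The loss is conditional.** It needs a positive ICC and, to be material, few therapists. Neither is given. Even that each therapist has several participants is an inference, although the alternative is about 64 therapists. This stands.
- **The ICC may be small.** Content comes from standardised online lessons. Guidance is messaging aimed at adherence, adds no therapeutic technique of its own, is supervised, and is stored for checking. This stands as a reason to expect a low ICC. It does not show that the ICC is zero.
- **The planned model may be more powerful than the one computed here.** Baseline adjustment could recover the loss, as Step 5 shows; an analysis of change scores at r = 0.5 would gain nothing. This stands for power. It does not repair the error rate of an analysis that ignores therapist.

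The sample-size statement is not touched by these points. It is fixed in the article, and a model term added later would not make that calculation account for nesting.

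**Conclusion.** The point holds in conditional form. The one-arm therapist grouping is stated, and N = 128 is exactly the independent-observations figure with no reserve. If the ICC is 0.02 to 0.05, power for the unadjusted comparison lies between 67% and 79% and the type I error of an analysis ignoring therapist between 5.5% and 9.5%, for 4 to 12 therapists. The upper end of the problem needs as few as 4 therapists with 16 participants each, which nothing in the article establishes; with many therapists and an ICC near 0.01 there is practically no effect. These figures rest on the assumptions listed in the working. The document does not show that the standard errors will be wrong or that the trial is underpowered. What it supports is a low-cost improvement to the analysis and a qualification of the power statement.

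**What to change.** - Keep therapist ID in the analysis dataset.
- Pre-specify, at least as a sensitivity analysis of the 6-week HRSD-24 comparison, a partially nested model: a therapist random effect in the GET.ON arm only, OPD participants as singletons, and small-sample degrees of freedom. Report the estimated ICC. With few therapists the variance component may be poorly estimated, which is a reason to keep this as a sensitivity analysis and not make it the primary model.
- Add to the sample size section that the 80% assumes no therapist clustering, and give power for ICC 0.02 to 0.05 at the actual number of therapists.

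The cost is one variance term and a sentence or two. Participants are already assigned to therapists and therapist feedback is stored, so no new data collection should be needed. The downside is a possibly wider interval and a less favourable power figure.
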